## Data collection and management

### Plans for assessment and collection of outcomes {18a}

After informed consent has been obtained (as described previously), a medical history, demographics, and subject eligibility will be reviewed:Medical history review

At screening, relevant medical history relating to inclusion/exclusion criteria will be reviewed by the study site staff to ensure that the participant meets all the inclusion criteria and none of the exclusion criteria. It is not necessary to collect participant medical history outside of eligibility criteria, except for any event that has occurred within 30 days prior to the participant’s screening visit or any ongoing medical history for which the participant is currently receiving a concomitant medication.2.Demographics

Participant demographics to be collected during the screening visit are as follows:RaceGender at birthRelevant contact detailsHeightWeight

3.Eligibility review

All participants will be reviewed for eligibility during the screening period and again at base line visit prior to randomization to ensure that they meet the eligibility to participate in this study.

Participants will also be assessed for the ability to perform the 30-Second Chair Stand Test utilizing correct technique at screening for study eligibility

A physical examination of the participant will then commence:Auscultation of the heart

At screening, the investigator or investigator’s delegate will auscultate the participant’s heart to review for heart murmurs that have not previously been detected.2.ECG

A single 12-lead ECG will be performed at screening to assess for arrhythmias that would exclude the participant from participating in the study. No further ECGs are required during the study period unless the investigator or investigator’s delegate deems it necessary clinically.3.Vital signs

All participants will have sitting blood pressure, pulse, and pulse oximetry performed at each on-site visit. If multiple readings are taken, the lowest should be recorded as data for the visit.

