## Participant timeline {13}

### Schedule of assessments

**Table Tabe:** 

Procedures and assessments	Visit 1	Visit 2	Visit 2a	Visit 3	Visit 4
	Screening	Baseline	Phone call	Interim assessment	EOS
	Day -28 to -1	Day 0	Within 6 days of baseline	Day 42±7	Day 91 +7
Informed consent	x				
Review of subject eligibility	x	x			
Demographics^1^	x				
Medical history	x				
Auscultate the heart to check for murmurs	x				
Vital signs^2^	x	x		x	x
ECG	x				
Hematology and biochemistry	x^3^			x^4^	x^3^
DNA methylation (TruDiagnostics)		x			x
SF-36 questionnaire		x			x
Assessment of ability to complete 30-Second Chair-Stand Test	x				
Randomization		x			
Allocation of weekly medication^5^		x		x	
Confirm participant day 1			x		
Weekly participant contact			x^6^		
Adverse event collection		x	x	x	x
Distribute subject diary card		x		x	
Collect subject diary cards				x	x
30-Second Chair-Stand Test		x		x	x
Hand grip strength		x		x	x
6-min walk test		x			x

^1^Race, gender at birth, contact details, height, and weight

^2^Resting heart rate, blood pressure, and oxygen saturation

^3^Full blood count, eGFR, urea and electrolytes, LFTs, HbA1c, lipids, IGF-1, hs-CRP

^4^Full blood count, LFTs, lipids

^5^Allocation of investigational product for 6-week period, followed by a 7-week period

^6^Participants are to be contacted by phone each week. Participants who cannot be reached following two phone contact attempts in a week can be sent a text message or email

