## Sample size {14}

The sample size was selected primarily to satisfy logistic constraints of this feasibility study. As this study is not confirmatory, we do not predicate the sample size primarily on power considerations: arm sizes of 20, assuming no withdrawals, will provide 80% and 90% power, respectively, to detect fairly large Cohen’s effect sizes of 0.8 and 0.9, respectively, at a nominal significance level of 0.1.

In regard to safety, the arm sizes and post-randomization follow-up time will enable to detect rate ratios of adverse events between the sirolimus (rapamycin) and placebo arms varying between 2.4 and 3.7, dependent upon the rate in the placebo arm and the dispersion of the data. Sample sizes of 12 per arm have been indicated as sufficient for pilot or feasibility studies [34]. However, our feasibility objective of variance estimation makes it preferable to aim for a total sample size of 40, as a 95% confidence interval for the variance will then have expected half-width of less than half the true variance, providing a reasonably precise estimate.

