## Assignment of interventions: blinding

### Who will be blinded {17a}

The study participants, care providers, outcome assessors, and data analysts will be blinded to the treatment groups. The trial statistician and CompoundLabs, who are not involved in the study activities at the site, will perform the randomization and code the blister packs of the drugs according to the allocation sequence.

Both sirolimus (rapamycin) and placebo capsules will be identical in appearance, taste, and packaging. CompoundLabs will allocate the active product capsules or placebo capsules into the blister packs with unique codes.

Adverse events will be reported and managed by blinded staff to ensure that the blinding is not compromised. Measures will be taken to maintain blinding throughout the study, including the use of a separate team for data analysis that is not involved in participant care or outcome assessment.

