### Data quality assurance

To promote data quality, assessors will receive training on standardized procedures for each outcome measure. Duplicate measurements will be taken when necessary to ensure accuracy. Data collection forms will be available in the protocol appendix for reference.

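### Keeping only the lowest of an unfixed number of vital-sign readings biases recorded blood pressure and pulse downward and under-counts high values

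*Protocol article*

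**What the plan says.** The vital-signs item under Plans for assessment and collection of outcomes {18a} sets the measures and visits: "All participants will have sitting blood pressure, pulse, and pulse oximetry performed at each on-site visit". It then gives the capture rule: "If multiple readings are taken, the lowest should be recorded as data for the visit". It states no number of readings, no trigger for a repeat and no reason for choosing the lowest.

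The Schedule of assessments places vital signs at screening, baseline, interim and end of study. Its second footnote defines them as "Resting heart rate, blood pressure, and oxygen saturation". The Secondary objectives section lists vital signs among the safety and tolerability measures.

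The only other text on repeats is under Data quality assurance: "Duplicate measurements will be taken when necessary to ensure accuracy". That leaves the decision to the assessor.

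**The concern.** The minimum of several noisy readings is not an unbiased estimate of a person's level. It is too low, and more so the more readings are taken. Because the number of readings is free, the size of the error can differ between people, between visits and possibly between arms.

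Three consequences follow for blood pressure and pulse:

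- Recorded levels are too low wherever a repeat was taken.
- A participant read once at baseline and twice at week 13 shows a fall with no true change. The reverse pattern shows a spurious rise.
- A high value is kept only if every reading at that visit was high. In a trial with "arm sizes of 20, assuming no withdrawals", individual high values are one of the ways in which a safety signal would show.

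This is not a detail left to an analysis plan. The rule fixes the visit value at data capture, before any analysis.

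**Working it through.** The plan gives no figure on this point, so there is none to reproduce. The documents also give no blood pressure distribution. The millimetre figures below are illustrations on assumed inputs; the SD multiples need only independent normal reading errors.

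**Bias of the minimum.** For k independent normal readings with within-visit SD s, the expected minimum lies below the true level by s/√π = 0.564s for k = 2, and by 3s/(2√π) = 0.846s for k = 3. With k = 2:

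- s = 4 mmHg: 0.564 × 4 = 2.3 mmHg too low
- s = 10 mmHg: 0.564 × 10 = 5.6 mmHg too low

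One reading at baseline and two at follow-up therefore give an apparent fall of 2.3 to 5.6 mmHg with no true change. This holds when the decision to repeat is unrelated to the reading.

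**Effect on the arm comparison.** Assumptions: systolic mean 135, between-person SD 15, true active-arm rise 5 mmHg, within-visit SD 4 to 10, two readings when repeated, 1,000,000 simulated participants per arm.

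*Policy A, everyone read twice.* The bias is the same at every level and in both arms. The mean arm difference stays at 5.0.

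*Policy B, second reading only if the first is at least 150.* The bias is about 0 at true levels of 110–120 and 2.2 to 5.6 mmHg at 160–170.

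| Within-visit SD | Repeated, placebo / active | Difference, lowest kept | Loss of the true 5.0 | Difference, mean kept |
|---|---|---|---|---|
| 4 | 16.7% / 25.9% | 4.76 | 5% | 4.97 |
| 6 | 17.6% / 26.7% | 4.61 | 8% | 4.92 |
| 8 | 18.9% / 27.8% | 4.48 | 10% | 4.88 |
| 10 | 20.3% / 29.0% | 4.37 | 13% | 4.84 |

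*A more aggressive policy:* two repeats if the first reading is at least 140, within-visit SD 7. Recorded means are 131.96 and 136.24, a difference of 4.28, so (5.0 − 4.28)/5.0 = 14% is lost. In the arm with mean 135, the share recorded at or above 140 is 25%, against 37% true. Using the mean of the readings gives 134.25 and 139.20, a difference of 4.95. Each arm is still 0.75 to 0.80 mmHg too low, because only high first readings were followed up.

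**High values.** The true shares at or above 160 are 9.1% in the active arm (mean 140) and 4.8% in placebo (mean 135), a difference of about 4.3 points. Keeping the lowest of two records 6.6 to 7.4% in the active arm and a difference of 3.0 to 3.6 points. Roughly 20 to 30% of the difference is lost, under either policy A or policy B.

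**The case against.** A reader might infer more than the text supports, in four ways.

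- *That the rule masks a drug-related rise.* It does not. The protocol states that "The study participants, care providers, outcome assessors, and data analysts will be blinded to the treatment groups", and the same rule applies at every on-site visit, so an equal shift cancels between arms and in change from baseline. With triggered repeats the loss is 5 to 14% of a 5 mmHg difference. On the aggressive policy's inputs, the standard error of an arm difference at 20 per arm is √(15² + 7²) × √(2/20) = 5.2 mmHg, so the 0.72 mmHg lost is about 0.14 of one standard error. Blinding does not rule out the attenuation, however: a drug that raises pressure would prompt more repeats even from fully blinded staff.
- *That the bias is largest where readings are high.* This needs repeats to follow high first readings. The protocol states no such trigger, and duplicates taken for accuracy could equally follow a low or implausible value.
- *That the loss cannot be undone.* The text says which reading becomes the visit value. It does not say that the others go undocumented, and Data management {19} requires source documents to be kept. They may survive there, though the rule does not make them trial data.
- *That the rule always leans towards no harm.* For oxygen saturation the lowest value is the unfavourable one, so harm is overstated. Low blood pressure and low pulse would also be over-counted.

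It is also fair to say that the safety analyses stated under Statistical methods {20a} model adverse-event counts and relatedness, not vital signs, and that investigators may judge adverse events on more than the recorded value. All of this limits the consequences. None of it makes the lowest reading a sound visit value.

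**Conclusion.** The concern holds as a defect in a stated data-capture rule for a listed safety measure. At visits with repeats, recorded blood pressure and pulse are too low by an average of 0.56 (two readings) or 0.85 (three readings) within-visit SD, given independent normal errors and repeats unrelated to the first reading. High values are under-counted, and unequal numbers of readings across visits produce spurious change.

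Attenuation of the mean arm difference is conditional and modest: about 5 to 14% of 5 mmHg if high first readings prompt repeats, and none if everyone has the same number. These percentages rest on assumed means, SDs and triggers. Visits with a single reading are not affected. Nor are the 30CST primary analysis, the sample size and the stated adverse-event models. The point is worth correcting because the correction is nearly free, but it does not threaten the trial's main conclusions.

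**What to change.** Replace the lowest-reading sentence with a rule for each vital sign:

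- Enter every reading in the eCRF.
- For blood pressure and pulse, use the mean of the visit's readings as the visit value.
- Preferably set the same number of readings for every participant at every visit. Averaging a triggered number leaves a small bias (4.84 to 4.97 of 5.0 under policy B); a fixed number removes it.
- State the rule for oxygen saturation separately, since its unfavourable direction is the opposite of that for raised pressure or pulse.

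The cost is a short text change and extra eCRF fields, plus a few more readings per visit if the number is fixed. If data have already been captured under the present rule, check whether the other readings can be recovered from source documents.

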### Provision of exercycle

Following participant randomization at the baseline visit, the participant’s contact details (name, mobile number, and/or email address) will be provided to Rutherford Fitness, the exercycle provider. Rutherford Fitness will arrange a suitable time with the participant for the delivery of the exercycle to the participant’s place of residence. The exercycle model provided will be BK838M exercycles (with a 120-kg maximum weight allowance), for the 13-week period of the study exercise intervention period, unless the participants withdraw early from the study. Exercycles will be delivered and installed and instruction provided to the participant by Rutherford Fitness. Exercycles will be collected at the end of the 13-week study exercise period at a time agreed with the participant. Should a participant wish to purchase or continue the bike hire at their own cost at the end of the 13-week study exercise period, the participant must inform the investigator or investigator’s representative by the end of week 10. The site will provide contact details to Rutherford Fitness to make arrangements directly with the participant.

### Weekly contact

All participants will be contacted by site staff weekly to check that study interventions are being completed. Contact should be made by phone call. If contact via phone call has been attempted twice in a single week without success, a text and/or email may be utilized that week. Each attempt is to be documented in the participant’s source documents.

Weekly phone calls are to include a brief discussion about the participant’s compliance with treatment dosing and the exercise program. Adverse events are to be discussed and documented by the study site staff.

If a participant has specifically requested contact be via text or email, the request is to be documented, and the participant’s preferred method of contact may be utilized, provided that the participant is responsive to the alternative method of contact regarding study compliance and adverse events.

## Primary outcome

30-Second Chair Stand Test (30CST): the 30CST is the primary objective measure for the study, assessing muscle strength and endurance. During screening, participants will be briefed on the test requirements and assessed for their ability to perform the 30CST to determine eligibility. The test will be conducted at baseline (visit 2), mid-intervention (visit 3), and post-intervention (visit 4). Participants will receive instructions on the correct technique prior to each assessment to ensure consistency. The test procedure will be standardized, and participants can refer to the guidance video available at: https://www.physio-pedia.com/30_Seconds_Sit_To_Stand_Test.

## Secondary outcomes

### Hand grip strength

This measure will be recorded for all participants at visits 2, 3, and 4 using a dynamometer to assess upper body strength. The participant’s dominant hand will be tested to ensure consistent and reliable results.

### 6-min walk test

The 6-minute walk test (6MWT) will be completed at baseline (visit 2) and end of study (visit 4) for all participants according to a standardized protocol:Setup

The test should be conducted on a straight 30-m track, with 1-m marker points delineating the track.

Equipment required is 6MWT recording form, pulse oximeter, stop-watch or timer, chairs at each end of the 30-m course, sphygmomanometer and stethoscope for measuring BP, trundle wheel to ensure the 6MWT is accurately marked out, clip board and recording sheet, and portable oxygen if required.

A chair(s) should be available should a participant need to urgently sit down.Conducting the test:

The 6MWT test must be administered according to the standard protocol provided to the site, ensuring that the test is completed in a similar manner each time for consistency and accurate measurements.

### Hematology and biochemistry

Non-fasting blood samples will be collected at screening (visit 1) and the end of the study (visit 4) for laboratory testing, including full blood count, eGFR, urea and electrolytes, liver function tests (LFTs), HbA1c, lipids, IGF-1, and hs-CRP. An interim safety sample for full blood count, LFTs, and lipids will be collected at visit 3. If samples are lost or damaged, participants will be asked to provide another sample within a week, except during the screening period where a 28-day period applies.

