#### Mechanistic target of rapamycin (mTOR)

mTOR is a protein kinase belonging to the phosphoinositide 3-kinase (PI3K)-related kinase family, forming two types of multiprotein complexes: mTORC1 and mTORC2 [3, 4]. Both complexes play vital roles in cellular regulation, and their dysregulation disrupts cell homeostasis, potentially leading to aging-related pathologies. Sirolimus (rapamycin) is a specific allosteric inhibitor of mTORC1, which plays critical roles in regulating mRNA translation, promoting lipid and nucleotide synthesis, and repressing catabolism and autophagy [5]. mTORC1 is highly sensitive to sirolimus (rapamycin), while mTORC2 is only inhibited after prolonged exposure [5].

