#### Preclinical evidence

There is abundant preclinical evidence that mTORC1 activity is a major driver of the biological aging process. In multiple organisms, genetic or pharmacological inhibition of the mTORC1 pathway has been shown to extend life and broadly delay molecular and functional declines associated with aging. These include genetic studies demonstrating that depleting mTOR or Raptor (a subunit of mTORC1) has life-extending effects in yeast [6], nematodes [7, 8], flies [9], and mammals [10], and similar outcomes when each of these organisms are treated with sirolimus.Mouse: sirolimus (rapamycin) treatment increases median and maximum lifespan when started at middle age (270 of 600 days of age) [11]. Treatment for only 3 months at middle age was sufficient to increase life expectancy by up to 60% and improve measures of health span in middle-aged mice [12]. Furthermore, sirolimus (rapamycin) treatment in mice was shown to increase alveolar bone levels [13], improve cardiovascular function [14–16], decrease body weight [17], and remodel the microbiome [12].Rat: sirolimus (rapamycin) treatment reduces food intake and body weight [16], increases grip strength, and attenuates the decline in maximum running distance [18]. Daily dosing in food did cause some diabetes-like symptoms [18], but repeated low doses do not seem to influence glucose homeostasis with long-term use [16].Dog: a study by Urfer et al. showed that low-dose (0.05 mg/kg and 0.10mg/kg) sirolimus (rapamycin) treatment three times a week over a period of 10 weeks in middle-aged dogs was well tolerated, with no clear adverse effects except for a decrease in the volume of red blood cells. The dogs had improvements in their left ventricular cardiac function and had increased activity [19].

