#### Clinical evidence

FDA-approved uses: sirolimus is approved for immunosuppression in organ transplant patients and cancer treatment, with higher doses associated with significant side effects including stomatitis, diarrhea, nausea, anemia, cytopenia, hyperglycemia, and hyperlipidemia, as well as the (intended) immunosuppressive effect.Low-dose studies: lower doses of sirolimus have shown safety in older populations. Studies have demonstrated well-tolerated doses with few mild side effects and improved immune function in elderly subjects [20–25].Exercise interaction: a study in young males found that sirolimus taken before resistance exercise impaired mTORC1 signaling and muscle protein synthesis, indicating the importance of timing sirolimus administration on non-exercise days [26].

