#### Selection of orally bioavailable rapamycin analogue

Although structurally similar, sirolimus and everolimus do not have identical effects on the mTOR pathway. Sirolimus primarily inhibits mTORC1, whereas everolimus is more effective at inhibiting mTORC2 at clinically relevant concentrations [27]. Life span-enhancing effects of mTOR inhibitors seen in preclinical models are predominantly linked to mTORC1 inhibition, while inhibiting mTORC2 might be detrimental, as mTORC2 controls insulin-mediated suppression of hepatic gluconeogenesis [28]. Therefore, sirolimus has been selected for this study as it preferentially inhibits mTORC1 without significantly affecting mTORC2.

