### Secondary objectives

There are several secondary objectives of this study as outlined below:To investigate the safety and tolerability of low-dose rapamycin in exercising older adults.

Safety and tolerability measures utilized to investigate the incidence, relatedness, seriousness, and severity of adverse events include:Clinical laboratory tests (full blood count, U&Es, LFTs, HbA1c, lipids, serum IGF-1)Vital sign measurementsAdverse events, serious adverse events, and events that impact exercise ability or dosing.

2.To evaluate change of muscle strength and muscle endurance from baseline to EOS Muscle strength and endurance measures will be evaluated by evaluating change from baseline in the:30-Second Chair-Stand Test (30CST)6-min walk testHandgrip strength

We will assess changes in upper body strength and cardiovascular endurance using grip strength and the 6-min walking test, respectively. The grip strength test will provide valuable insights into the impact of the intervention on muscular strength and function, critical for daily activities and autonomy in the elderly. The 6-min walking test will evaluate alterations in aerobic capacity and endurance, indicative of the participants’ ability to perform sustained physical activities.3.Participant-reported outcomesChange from baseline in the self-reported measures of health status and quality of life as determined by the 36-Item Short Form Survey (SF-36) through EOS.

The validated SF-36 tool provides measurement of the intervention’s impact from the participants’ perspective, encompassing aspects such as pain, general health perceptions, physical functioning, emotional well-being, and social functioning.

Participant self-reported physical activity, from baseline to EOS via participant diary.

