#### Exclusion criteria

Anemia—Hg < 9.0 g/dl, leukopenia—white blood cells (WBC) < 3500/mm3, neutropenia—absolute neutrophil count < 2000/mm3, or platelet count—platelet count < 125,000/mm3.Planned surgery during the study period that impacts the ability to perform required study exercises.Any medical or psychological condition which, in the opinion of the investigator, may interfere with the participant’s ability to comply with the study and/or put the participant at significant risk.Impaired wound healing or history of a chronic open wound.Active infection at the time of signing consent or taking antibiotics or antifungal medications.Malignancy (except non-melanoma skin cancers, cervical carcinoma in situ) within the last 5 years.Known hypersensitivity, allergy, or any contraindication to sirolimus (rapamycin) or placebo (cellulose powder) or its excipients.Fibromyalgia, chronic fatigue syndrome/myalgic encephalomyelitis, breast implant illness, or other conditions that impact the participant's ability to perform the exercise program.Known congestive heart failure with New York Heart Association (NYHA) classification III or IV.Prescribed substances that inhibit or induce CYP3A4 and/or P-glycoprotein (P-gp).Current prescribed or reported cannabinoid use.COPD Global Initiative for Chronic Obstructive Lung Disease (GOLD) classification III or IV.Impaired renal function defined as glomerular filtration rate (eGFR) < 30.Type 1 diabetes or uncontrolled type 2 diabetes (defined as HbA1c ≥60 mmol/mol).Metformin, sirolimus (rapamycin), or rapalogs use within 6 months prior to baseline.Impaired hepatic function measured by alkaline phosphatase (ALP), alanine aminotransferase (ALT), albumin, or T. Bili whereby the levels are 1.5× greater than the normal upper limit.Any form of clinically relevant primary or secondary immune dysfunction or deficiency (e.g., X-linked agammaglobulinemia (XLA), common variable immunodeficiency (CVID)).Chronic oral corticosteroid or immunosuppressive medication use (e.g., Enbrel, Humira, methotrexate, ciclosporin).Participation in any other study (for 30 days) prior to or during this study.

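### The Visit 3 safety sample has no glycaemic test, so the first on-treatment HbA1c comes after 12 or 13 of the 13 doses (minor, participant safety only)

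*Protocol article*

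**What the plan says.** The interim panel is stated in three places of the protocol article, and they agree. The section Hematology and biochemistry reads: "An interim safety sample for full blood count, LFTs, and lipids will be collected at visit 3". Footnote 4 of the Schedule of assessments gives the same three items, and so does the section on biological specimens {33}. HbA1c is part of the larger panel in footnote 3, which is run at screening and Visit 4. No glucose test appears at any visit.

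Other sections bear on glycaemia:

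- Clinical evidence describes sirolimus "with higher doses associated with significant side effects including stomatitis, diarrhea, nausea, anemia, cytopenia, hyperglycemia, and hyperlipidemia".
- Secondary objectives counts HbA1c among the safety and tolerability measures: "Clinical laboratory tests (full blood count, U&Es, LFTs, HbA1c, lipids, serum IGF-1".
- Exclusion criteria removes "Type 1 diabetes or uncontrolled type 2 diabetes (defined as HbA1c ≥60 mmol/mol", so type 2 diabetes below that value can enter. Metformin use within 6 months is also excluded.
- Three background sections are reassuring about a low or intermittent dose. The mTOR section says "mTORC1 is highly sensitive to sirolimus (rapamycin), while mTORC2 is only inhibited after prolonged exposure". Preclinical evidence reports diabetes-like signs in rats dosed daily, "but repeated low doses do not seem to influence glucose homeostasis with long-term use". The section on choice of analogue prefers sirolimus because it largely spares mTORC2, where "mTORC2 controls insulin-mediated suppression of hepatic gluconeogenesis".

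**The concern.** The article names laboratory side effects in three domains at higher doses: blood count, lipids and glucose. The interim sample checks the first two, adds liver function, and leaves out the third. A safety sample taken in mid-treatment is there to find changes the participant cannot feel while dosing can still be altered. For glucose, the schedule has no such test.

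Weekly contact and the informed general practitioner can pick up symptomatic hyperglycaemia, but neither schedules a test for an asymptomatic rise. If such a rise is first seen at Visit 4, the result adds to the trial's safety data but comes too late to guide that participant's dosing. The participants most exposed are those who enter with type 2 diabetes below the exclusion threshold.

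**Working it through.** The plan gives no figure of its own here. The check counts doses taken before each possible glycaemic result.

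**Inputs**

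- Week 1 Day 1 falls on study day s = 1 to 6 (Participant activities schedule).
- The weekly dose is taken on Day 6 of each week, for 13 weeks (dosing schedule).
- Visit 3 is on Day 42 ± 7, that is Day 35 to 49. Visit 4 is on Day 91 + 7, that is Day 91 to 98 (Schedule of assessments).
- Supply is issued for 6 weeks at baseline and for 7 weeks at Visit 3 (footnote 5).

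**Formula.** Dose k falls on study day s + 5 + 7(k − 1).

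- First dose (k = 1): Day 6 (s = 1) to Day 11 (s = 6).
- Last dose (k = 13): Day 90 (s = 1) to Day 95 (s = 6).

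**As planned: first on-treatment result at Visit 4**

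- Days since the first dose: 91 − 11 = 80 to 98 − 6 = 92.
- Doses taken: 12 if Visit 4 comes before dose 13 (for example s = 6, Visit 4 on Day 91, dose 13 due on Day 95), otherwise 13.
- Doses left: 0 or 1.

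**With a test at Visit 3**

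- Days since the first dose: 35 − 11 = 24 to 49 − 6 = 43.
- Doses taken: at least 4 (s = 6, Visit 3 on Day 35, doses on Days 11, 18, 25 and 32). The dates alone allow 7 (s = 1, Visit 3 on Day 49), but the 6-week supply caps this at 6.
- Doses left at the draw: 13 − 6 = 7 to 13 − 4 = 9.
- Doses left once acted on, assuming this happens at the next weekly contact, within 7 days and after about one more dose: 7 − 1 = 6 to 9 − 1 = 8.

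**Sensitivity.** Ignoring the supply cap, 13 − 7 = 6 to 9 doses remain at the draw, or 5 to 8 after one more. Letting Week 1 Day 1 fall on study day 0, or counting a dose taken on the visit day, still gives 12 to 13 doses before Visit 4.

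**Why the entry threshold alone is a poor trigger.** Reaching 60 mmol/mol needs a rise of 60 − 40 = 20 from a screening value of 40, 60 − 50 = 10 from 50, and 60 − 59 = 1 from 59. The threshold alone would miss large rises in some participants and flag trivial ones in others.

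**The case against.** The strongest reply is that the panel is a deliberate, internally consistent choice that the article's own text supports. Hyperglycaemia is tied to higher doses, and low doses are described as well tolerated in older people. The rat signal came with daily dosing. With the stated half-life of 64 h, about 0.5^(168/64) = 16% of a dose remains when the next is due, so exposure is intermittent. The low-dose dog study was summarised "with no clear adverse effects except for a decrease in the volume of red blood cells", which supports spending the interim sample on the blood count. The test proposed is also imperfect: HbA1c 24 to 43 days after the first dose shows only part of a change, and a non-fasting glucose is noisy. No incidence is given, so no number of participants harmed can be derived.

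Most of this stands. It rules out calling the panel an error or a contradiction, and it keeps the grade at the lowest level. It does not close the gap. The glucose-specific reassurance is rat data and mechanism, and the human low-dose summary is general. End-of-study HbA1c and symptom reports leave an asymptomatic rise untested while dosing continues. A partly sensitive result with several doses left is more useful to the participant than a fuller one with none or one left.

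**Conclusion.** The point holds as a minor, inexpensive improvement for participant safety. No glycaemic test is scheduled between screening and Visit 4, and 12 or 13 of the 13 doses, over 80 to 92 days, precede the first on-treatment result. A Visit 3 test would leave 6 to 8 doses open to change, given the 6-week supply cap and action within a week.

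Expected risk at this dose is low on the article's own account and cannot be quantified from it. The number of the 40 participants who will have type 2 diabetes is not given, and the exclusions narrow it. The primary analysis and the 13-week HbA1c comparison between arms do not change.

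**What to change.** Add HbA1c to the Visit 3 panel in three places: the interim-sample sentence under Hematology and biochemistry, footnote 4 of the Schedule of assessments, and the interim-sample sentence in section {33}. A random glucose from the same draw is optional.

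Set an action rule in advance. Blinded site staff compare the result with the participant's screening value. Either of two findings goes to the principal investigator, as section {11b} already requires for stopping treatment because of adverse events:

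- a rise from screening of a size the sponsor fixes beforehand (the documents give none; 5 to 10 mmol/mol is an assumed range), or
- a value of 60 mmol/mol or more, confirmed on repeat.

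The second supply is handed out at the same visit as the draw, so any dosing change has to go through the weekly contact once the result is back.

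The cost is at most 40 routine assays on blood already taken, with no extra visit or needle for the first test, plus edits to two sentences and one footnote. Some confirmatory repeats will be needed, and a smaller trigger brings more false alarms; the documents do not allow their number to be estimated. Staff should be told that a normal Visit 3 value does not exclude an effect.
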